### Study design

#### Description of research design

This is an open‐label, prospective, single‐center, single‐arm, exploratory clinical trial to observe and evaluate the efficacy and safety of continued apatinib combined with EGFR‐TKI in NSCLC patients with slow progression after EGFR‐TKI monotherapy.

#### Overall study design

This research will be conducted in a single center, in the lung cancer surgery department of Tianjin Medical University General Hospital. Patients will be withdrawn from the study for any of the following reasons:Withdrawal of consentDrug toxicity or intoleranceThe principal investigators considers the patient is unfit to continue in the study.

During the study, patients will undergo imaging to monitor tumor progression. Efficacy and safety endpoints will be monitored throughout the study.

#### Experimental drugs

Name: Apatinib

Specification of preparation: 0.25 g (10 tablets/plate/box)

Preparation unit: Jiangsu Hengrui pharmaceutical co., Ltd

Validity period: 24 months

Route of administration: oral administration

Storage conditions: shading, sealing, below 25°C

#### Patient selection and inclusion criteria

Diagnostic criteria: the diagnosis will be confirmed according to the sixth edition of Oncology Diagnostics and the eighth edition of Internal Medicine published by the People's Medical Publishing House of the People's Republic of China.

#### Inclusion criteria

Males or females ˃18 years old and <80 years old.Diagnosed with advanced stage (IIIB or IV), nonsquamous NSCLC, with measurable lesions (per RECIST 1.1 criteria).NSCLC patients with slow progression determined by (i) disease control lasting ≥3 months with EGFR‐TKI treatment, (ii) compared with the previous assessment, no significant increment of tumor burden and progressive involvement of nontarget lesions with a score ≤2, or PD due to solitary extracranial lesion or limitation in intracranial lesions (covered by a radiation field), or the abnormal CEA level is increasing higher than pre‐EGFR‐TKIs treatment during the last three months with a score ≤2, and (iii) symptom scored ≤1.There is no interventional systemic treatment between cessation of gefitinib or erlotinib and initiation of new treatment.Eastern Cooperative Oncology Group (ECOG) performance status (PS) score: 0–2.Expected survival ≥12 weeks.No previous chemotherapy or other targeted therapy. For patients with chemotherapy as first‐line treatment and EGFR‐TKIs as second‐line treatment.Patients may have been treated with radiation previously, but the radiation area must be less than 25% of the bone marrow area^15^ and radiation therapy must end at least four weeks before being enrolled into the group.Main organs are functioning normally (ie, no blood transfusion or blood products within 14 days, no correction with granulocyte‐colony stimulating factor and other hematopoietic stimulators):Blood routine test must be:Hemoglobin ≥90 g/LAbsolute neutrophil count ≥1.5 × 10^9^/LPlatelets ≥80 × 10^9^/L or higher
Blood biochemical tests must be:Total bilirubin <1.5 × upper limit of normal (ULN)Alanine aminotransferase and aspartate aminotransferase <2.5 × ULN or <5 × ULN in patients with liver metastasisSerum creatinine ≤1.25 × ULN or endogenous creatinine clearance >45 mL/minute
Females of reproductive age must have a negative pregnancy test (serum or urine) within seven days prior to enrollment and voluntarily use appropriate methods of contraception during observation and for eight weeks after the last apatinib tablet. Males must be surgically sterilized or voluntarily consent to use appropriate contraceptive methods during the observation period and for eight weeks after the last apatinib tablet is given.Patients volunteered to participate in this study and signed the informed consent (ICF), with good compliance and follow‐up.

#### Exclusion criteria

Persistent clinical treatment‐related toxicity associated with previous chemotherapy and/or radiotherapy.Receive radiotherapy (except for limbs and brain) within three months prior to baseline imaging examination.Symptomatic brain metastases (patients with brain metastases who have completed treatment 21 days before enrollment and are confirmed to have no symptoms of cerebral hemorrhage and stable symptoms can be enrolled).Radiological evidence suggests the presence of vacuous or necrotizing tumors.Imaging shows that the distance of the primary tumor from the great blood vessel is ≤5 mm; or the primary tumor invaded the local great blood vessel; or have obvious lung cavity/necrotizing tumor.Coagulant function abnormality (international normalized ratio > 1.5 × ULN, or activated partial thromboplastin time > 1.5 × ULN) with bleeding tendency, or is treated with thrombolysis and anticoagulation and antiplatelet drugs, including obvious hemoptysis/daily hemoptysis of two teaspoons or above within two months of enrollment, clinically significant bleeding or bleeding tendency within three months of enrollment, venous thromboembolism events within one year of enrollment, or known other inherited or acquired bleeding and thrombosis tendency.Patients with hypertension who do not drop to the normal range after antihypertensive medication (systolic blood pressure > 140 mmHg, diastolic blood pressure > 90 mmHg).Long‐term open wounds/fractures.˃level II or poorly controlled cardiovascular disease.Squamous cell carcinoma (including adenosquamous cell carcinoma); small cell lung cancer (including mixed small cell and non‐small cell lung cancer).Patients with a history of interstitial lung disease or who also have interstitial lung disease.In the judgment of the principal investigators has any other conditions that might influence the outcome of the study.

#### Criteria for excluding patients from analysis

Study drugs were not taken in accordance with the protocol, making it impossible to evaluate efficacy and/or safety.

## Serious protocol violations

#### Patient withdrawal criteria

Patient withdraws informed consentMedical imaging examination shows PDPregnancy during the trialPrincipal investigator discretion

### Dosage regimen

Apatinib: 250 mg orally, once daily; EGFR‐TKI: dose determined by principal investigator.

### Clinical data collection

#### Screening period (14 days before treatment)

Once the patient signs the ICF, they will undergo the following evaluations: medical history collected, vital signs, physical examination and blood pressure, coagulation function, electrocardiogram (ECG), ECOG PS score, routine blood tests, routine urine tests, routine stool tests, liver and kidney function, electrolyte, tumor markers, biomarkers, CEA, imaging examination (computerized tomography [CT]/magnetic resonance imaging [MRI]).

### During treatment (every four weeks for a cycle, every two cycles for the efficacy evaluation)

#### Singular period

Patients will undergo the following evaluations: vital signs, physical examination, blood pressure, coagulation function, ECG, ECOG PS score, routine blood tests, routine urine tests, routine stool tests, liver and kidney function, electrolyte, tumor markers, biomarkers, CEA, QoL score, adverse events, and concomitant medication.

#### Even period

Patients will undergo the following evaluations: vital signs, physical examination, blood pressure, QoL score, adverse events, and concomitant medication.

#### After treatment (within 30 days after the end of treatment)

Patients will undergo the following evaluations: adverse events, concomitant medication and QoL.

## Safety parameters

### Adverse events observation

#### Adverse event definition

Adverse events are any adverse medical events that occur after a subject or clinical trial subject receives a drug or treatment regimen but are not necessarily cause‐and‐effect.

Adverse events may be any signs (including abnormal laboratory results), symptoms, or diseases that are unpleasant or unrelated to the purpose of the use of the product and that have a temporal association with the use of the product, whether or not they are considered to be related to the medical product.

According to the regulations, events that occur before and after treatment are also considered adverse events. Therefore, reports of safety monitoring adverse events or serious adverse events should begin when subjects enter the trial (after signing the ICF and passing screening) and continue until the final follow‐up visit.

#### Adverse event classification

Adverse events will be classified by CTCAE version 4.0, according to the National Cancer Institute (NCI) standard of classification for common acute and subacute toxicity. Adverse events not listed in the NCI toxicity classification criteria can be judged according to the following criteria:Degree 1 (mild): uncomfortable feeling, but does not affect normal daily activitiesDegree 2 (moderate): the level of discomfort is not enough to reduce or affect normal daily activitiesDegree 3 (severe): inability to work or normal daily activitiesDegree 4 (fatal): disabling or fatal

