### Secondary endpoints

Overall survival (OS): time from randomization to death from any cause.Objective response rate (ORR): refers to the proportion of patients whose tumor shrinkage has reached a certain level and maintained for a certain period of time, including cases of complete response (CR) and partial response (PR). RECIST 1.1 criteria were used to evaluate objective tumor remission. The patients must have measurable tumor lesions at baseline. According to RECIST 1.1, the evaluation criteria of efficacy can be divided into CR, PR, SD and PD.Disease control rate (DCR): refers to the percentage of patients with confirmed CR, PR and disease stability (≥4 weeks) in the patients with evaluable efficacy.Quality of life score (QoL), refers to the EORTC QLQ‐C30 (version 3, Chinese version) evaluation method. The questionnaire evaluates changes in clinical symptoms and objective examination results of tumor patients before and after treatment. The results of each field of the QoL scale will be recorded in the electronic case report form (eCRF).Drug safety: patients will be monitored for adverse events occurring during the period of clinical research. In addition, patients will undergo clinical laboratory tests, and clinical characteristics will be monitored, including severity, occurrence time, duration, treatment and prognosis. Any correlation between experimental drugs will be documented. Common Terminology Criteria for Adverse Events (CTCAE) version 4.0 will be used to categorize adverse events.

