#### Recording adverse events

Details of adverse events during the trial, including severity, time, duration, and relation to study treatments will be recorded in the eCRF. Abnormal laboratory results will recorded in the eCRF, and will be followed up at least weekly until the abnormal result normalizes or the study is completed.

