#### Serious adverse event

If any Serious Adverse Event (SAE) occurs during the trial, the investigator should immediately take appropriate measures to protect the patients and report the SAE to the principal investigator within 24 hours. The investigator should fill in the SAE report form, sign and date the report. SAEs events include: death or life‐threatening; cause or prolong hospitalization; cause permanent disability; cause cancer: cause deformity: drug overdose.

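### In the fallback severity scale, degree 2 (moderate) repeats degree 1, so an event that limits but does not prevent daily activity has no degree; degree 4 is labelled fatal but includes survivors

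*Protocol article*

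**What the plan says.** The section Adverse event classification names the main system first: "Adverse events will be classified by CTCAE version 4.0". It then supplies a scale for the remainder: "Adverse events not listed in the NCI toxicity classification criteria can be judged according to the following criteria". Its four degrees are:

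- Degree 1: "mild): uncomfortable feeling, but does not affect normal daily" activities.
- Degree 2: "moderate): the level of discomfort is not enough to reduce or affect normal daily" activities.
- Degree 3, labelled severe: the patient is unable to work or to carry out usual daily activities.
- Degree 4: "fatal): disabling or fatal".

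The grade is a recorded data item. Under Recording adverse events: "Details of adverse events during the trial, including severity, time, duration, and relation to study treatments will be recorded in the eCRF". Drug safety is a secondary endpoint, and the Secondary endpoints section says that "clinical characteristics will be monitored, including severity, occurrence time, duration, treatment and prognosis". The Statistical analysis plan section summarises adverse events with descriptive statistics only. No other section restates or corrects the four definitions.

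**The concern.** A severity scale should give each event one degree. Here the definition of the second degree works against its own label. An event called moderate, placed between mild and severe, is defined as one that leaves daily activity unaffected, and that is already the definition of mild. The grader has no rule for choosing between degrees 1 and 2, and no degree for the level in between.

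The top degree has a separate labelling fault. Its name says fatal, but its definition admits patients who survive with a disability.

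What is at stake is whether the severity grade can be reproduced and read correctly for unlisted events. Two investigators who follow the text faithfully could grade the same event differently, and a severity table could show a survivor in a row headed fatal. In an open-label, single-arm study planning 38 patients, safety rests on descriptive tables of this kind.

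**Working it through.** No figure is involved, so the check is logical. Take the possible levels of effect on the patient, in order, and see which printed degrees each one satisfies.

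| Effect of the event | Degrees that fit as printed | Result |
|---|---|---|
| Discomfort, daily activity unaffected | 1 and 2 | Two degrees, no rule to choose |
| Daily activity limited, not prevented | None | Excluded by 1 and 2; 3 requires inability |
| Unable to work or do daily activities | 3 | Assignable |
| Disabled, alive | 4 | Assignable, but under the label fatal |
| Death | 4 | Same degree and label as a disabled survivor |

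**Degrees 1 and 2.** Degree 1 excludes any effect on daily activity ("mild): uncomfortable feeling, but does not affect normal daily"). Degree 2 excludes any reduction or effect ("moderate): the level of discomfort is not enough to reduce or affect normal daily"). Any event whose discomfort leaves activity unaffected meets both, and any event that affects activity meets neither.

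**The gap.** Degree 3 begins at inability. Everything between no effect and inability is therefore left out.

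**Degree 4.** The label and the definition ("fatal): disabling or fatal") do not cover the same patients, because the definition is wider than the label.

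**Check of the repair.** If degree 2 is turned round to mean that activity is limited but not prevented, row 1 maps to degree 1 only, row 2 to degree 2 only and row 3 to degree 3 only. One change of wording removes both the overlap and the gap. The clause saying that activity is not prevented is needed, because inability is also an effect on activity and would otherwise meet degree 2 as well as degree 3. The degree 4 label is not touched by this change and needs its own correction.

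**The case against.** The strongest reply is that this is one misplaced negative, probably a drafting or translation slip, in a fallback scale of little reach. The ordered labels mild, moderate and severe show the intended ranking, CTCAE 4.0 is the main system, and the fallback wording is permissive. In this document no withdrawal criterion, analysis set or hypothesis test uses a severity grade. All of that stands, and it is why the point is minor. It does not remove the point, because the printed text is the rule a grader would follow and it reverses the meaning of one degree.

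Several stronger readings are tempting, and the document does not support them:

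- **All grades from the scale are wrong.** Degree 3 can still be assigned, and the ranking is clear from the labels. The fault lies between degrees 1 and 2, in the gap above them, and in the degree 4 label.
- **The Serious adverse event section contradicts the scale.** Its list runs "death or life‐threatening; cause or prolong hospitalization; cause permanent disability". Death and life-threatening events form one item there, so it does not keep all three outcomes apart. It also defines seriousness, a different attribute from severity, and may group outcomes differently.
- **A survived life-threatening event has no degree.** Such a patient would ordinarily be unable to work or carry on daily life, and so meets degree 3.
- **Deaths cannot be identified.** A severity column based on this scale would not separate them, but the trial data would: death is a PFS event, the OS event, and reportable as a serious adverse event within 24 hours.
- **The grades cannot be combined with CTCAE grades.** The document does not reproduce the CTCAE grade definitions, so this cannot be settled from it.
- **A given number of records is affected.** The document states neither an expected number of events nor the share that falls outside CTCAE.

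**Conclusion.** The point holds in a narrow form and is minor. As printed, degree 2 of the fallback scale contradicts its label and duplicates degree 1, so an event that limits but does not prevent daily activity cannot be graded. Secondarily, degree 4 calls disabled survivors fatal.

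The size can be stated only by its limits: unlisted events, in descriptive safety summaries. PFS, the other efficacy results and all CTCAE-graded events are unaffected. The conclusion assumes only that the published definitions are the ones in use. If the working protocol or eCRF already carries corrected wording, the article alone needs an erratum.

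**What to change.** 1. Reword degree 2 as discomfort that limits usual daily activity but does not prevent it.
2. Relabel degree 4 so that its name covers both disabling and fatal outcomes and does not describe survivors as fatal.
3. In the severity table, report deaths separately from disabling events. A fifth degree is one way to do this but is not required.
4. Before database lock, check any unlisted events already graded against the corrected wording, and regrade where needed.

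The cost is a few lines of protocol text, a matching change to the eCRF code list if it carries the same wording, and a review of whatever unlisted events exist. The Ethical considerations section requires ethics committee approval before a protocol modification is implemented, so the change goes through that route. No analysis method or sample size changes.

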#### Recording adverse events

Details of adverse events during the trial, including severity, time, duration, and relation to study treatments will be recorded in the eCRF. Abnormal laboratory results will recorded in the eCRF, and will be followed up at least weekly until the abnormal result normalizes or the study is completed.

#### Judgment of the relationship between adverse events and study drugs

Relationship between adverse events and study drugs will be categorized as follows.

#### May be related

Consistent with the known type of reaction to the drug used, consistent with a reasonable sequence of time after administration, reduced or reduced or disappeared after withdrawal of the drug, but the patient's clinical status or other reasons may also cause this reaction.

#### May be not related

It does not conform to the known type of reaction of the drug used, does not conform to the reasonable time sequence after the drug is administered, and the patient's clinical status or other reasons may also cause the reaction.

#### Not related

It does not conform to the known type of reaction of the drug used, does not conform to the reasonable time sequence after the use of the drug, the patient's clinical state or other reasons can also explain the reaction, and the reaction is reduced or disappeared after excluding clinical symptoms or other reasons.

#### Indeterminable

The relationship between drugs used and adverse reactions cannot be explained.

#### Serious adverse event

If any Serious Adverse Event (SAE) occurs during the trial, the investigator should immediately take appropriate measures to protect the patients and report the SAE to the principal investigator within 24 hours. The investigator should fill in the SAE report form, sign and date the report. SAEs events include: death or life‐threatening; cause or prolong hospitalization; cause permanent disability; cause cancer: cause deformity: drug overdose.

#### Observation and management of adverse events

The study center is equipped with first‐aid drugs, oxygen, blood pressure meter, electrocardiograph, defibrillator, ventilator, and a series of drugs and equipment needed for routine infusion. Patients will be given the study drugs under the supervision of a clinician, and their vital signs and other adverse reactions will be observed periodically until the end of the study. According to different conditions of adverse events and SAEs, appropriate treatment measures will be taken for patients, and necessary rescue measures will be adopted in case of emergencies.

#### Management of adverse reactions

Generally, after the occurrence of minor adverse reactions, the clinician should first observe the condition, make a clear diagnosis and determine the prognosis. If the study is not affected, observation and symptomatic treatment and other measures should be taken to try to improve, cure or stabilize the reaction.

## Statistical methods

### Data management

The CRF should be completed by the principal investigator for each patient, and checked to ensure complete and accurate. After reviewing and confirming that the data is correct, key researchers, sponsors and statistical analysts will lock the database. After this point, no changes will be made to the locked data file.

### Statistical analysis of data

#### Data sets

There will be three sets of analyses in this study as follows.

#### Full analysis set

This will be comprised of all patients who receive at least one dose of the study drug. Data from the last observation carried forward (LOCF) will be used in cases where the full course of treatment was not observed.

#### Per protocol set

This will be comprised of all patients who conform to the study protocol, have good compliance, do not take prohibited drugs during the study, and have complete eCRFs. There will be no input of missing data in this data set.

#### Safety analysis set

This will be comprised of all patients who receive at least one dose of study drug and have any safety information recorded. This data set will be used for security analysis.

### Statistical analysis plan

All statistical analysis will be performed by SPSS 19 statistical analysis software. All statistical tests will be performed by bilateral test. *P*‐values ≤0.05 will be considered statistically significant, and the 95% confidence interval reliable.

Baseline data will be analyzed according to the full analysis set, and all efficacy indicators will be analyzed according to the full analysis set and the per protocol set. Security analysis will be performed using the safety analysis set.

Abscission analysis: descriptive analysis will be used to compare of total abscission rate. Abscission rate due to adverse events will be performed using a chi‐square test or Fisher's exact probability test.

Efficacy analysis: for indicators PFS and OS, the product limit method will be adopted and 25%, 50% (median), 75% PFS and OS at different times after treatment will be calculated, respectively according to the actual situation of the data.

Safety analysis: descriptive statistics will be used to describe the adverse events in this study. Laboratory test results will be summarized using descriptive statistics.

